## Abstract

**Background:**

In 2020, an estimated 287 000 women died globally from pregnancy‐related causes and 2 million babies were stillborn. Many of these outcomes can be prevented by quality healthcare during pregnancy and childbirth. Within the continuum of maternal health, antenatal care (ANC) is a key moment in terms of contact with the health system, yet it remains an underutilized platform. This paper describes the protocol for a study conducted in collaboration with Ministries of Health and country research partners that aims to employ implementation science to systematically introduce and test the applicability of the adapted WHO ANC package in selected sites across four countries.

**Methods:**

Study design is a mixed methods stepped-wedge cluster randomized implementation trial with a nested cohort component (in India and Burkina Faso). The intervention is composed of two layers: (i) the country- (or state)-specific ANC package, including evidence-based interventions to improve maternal and newborn health outcomes, and (ii) the co-interventions (or implementation strategies) to help delivery and uptake of the adapted ANC package. Using COM-B model, co-interventions support behaviour change among health workers and pregnant women by (1) training health workers on the adapted ANC package and ultrasound (except in India), (2) providing supplies, (3) conducting mentoring and supervision and (4) implementing community mobilization strategies. In Rwanda and Zambia, a fifth strategy includes a digital health intervention. Qualitative data will be gathered from health workers, women and their families, to gauge acceptability of the adapted ANC package and its components, as well as experience of care. The implementation of the adapted ANC package of interventions, and their related costs, will be documented to understand to what extent the co-interventions were performed as intended, allowing for iteration.

**Discussion:**

Results from this study aim to build the global evidence base on how to implement quality ANC across different settings and inform pathways to scale, which will ultimately lead to stronger health systems with better maternal and perinatal outcomes. On the basis of the study results, governments will be able to adopt and plan for national scale-up, aiming to improve ANC nationally. This evidence will inform global guidance.

Trial registration number: ISRCTN, ISRCTN16610902. Registered 27 May 2022. https://www.isrctn.com/ISRCTN16610902

## Background

In 2020, an estimated 287 000 women died globally from pregnancy‐related causes and 2 million babies were stillborn, half occurring during the third trimester [1, 2]. Many of these adverse outcomes can be prevented by quality healthcare during pregnancy and childbirth. Within the continuum of maternal health, antenatal care (ANC) is a key moment in terms of contact with the health system, yet it remains an underutilized platform [3, 4]. Implementing timely and appropriate evidence‐based practices during ANC can improve maternal and fetal health [5, 6]. Recent evidence shows that while most (more than 80%) women receive at least 1 ANC visit, only 49.3% receive 4–7 visits, and 11.3% received 8 ANC visits in low- and middle-income countries (LMICs) [7]. This was especially due to late initiation, as most women (50.1%) had their first visit after their first trimester [8].

To improve maternal health and outcomes, the WHO released its comprehensive recommendations on ANC for positive pregnancy experience in 2016 [9]. The guideline is intended to prioritize person-centred care and wellbeing, not only the prevention of death and morbidity [10]. It includes recommendations related to antenatal nutrition, maternal and foetal assessments, preventative measures, interventions for common physiological symptoms (e.g. nausea, heartburn, constipation), as well as health systems interventions to improve ANC utilization and quality of care for a consolidated package of routine ANC. Despite the value of guidelines for setting standards in healthcare provision, applying these recommendations within local contexts and at point of care is a well-documented challenge, including for maternal health [11–16]. Additionally, variability and complexity of local conditions require adaptations of the global guidelines, thus driving WHO to develop new efforts to assist countries in adapting and implementing the ANC recommendations. Finally, the use of implementation science, informed by theories and frameworks, to help promote evidence-based interventions in LMICs, has been limited [17, 18].

Since February 2018, the governments of Burkina Faso, Rwanda and Zambia, as well as Assam and Tamil Nadu states in India, have prioritized the adaptation and adoption of the WHO ANC recommendations. Initial efforts lead to the development of the WHO ANC recommendations adaptation toolkit [19]. Governments and stakeholders employed the toolkit to adapt the ANC package and update national- and state-level ANC policies. As a next step, this protocol outlines implementation research, applying the Capability Opportunity Motivation-Behaviour (COM-B) model for behaviour change to design co-interventions, and the theoretical framework of acceptability, to better understand what it will take to provide quality, integrated and person-centred ANC packages [20, 21]. In Rwanda and Zambia, this will include the deployment of a country-adapted digital intervention (WHO digital ANC module) to support the implementation of their ANC packages [22], in line with national digital health strategies [23] and the WHO’s SMART guideline approach [24].

In collaboration with Ministries of Health (MoHs) and country research partners, the study uses implementation science to systematically introduce and test the applicability of the adapted ANC package in selected sites across four countries. It aims to generate key evidence on the implementation of the adapted ANC packages and inform future national adaptation and scale up. Study objectives are outlined in Table 1; in Rwanda and Zambia, there will be a formative phase.

**Table 1 Tab1:** Study objectives

Burkina Faso and India
*Primary objectives*
1. Does the adherence to the country/state package of ANC interventions by health workers improve with the country/state-specific ANC package? a. Does the implementation of country/state-specific ANC package (including targeted community mobilization) increase early initiation of ANC among pregnant women? 2. Is the country/state-specific ANC package acceptable to and does it create value for women and health workers?
*Secondary objectives*
1. What are the human resources training and supervision needs of implementing the country/state-specific ANC package? 2. What is the cost of implementing the country/state-specific ANC packages compared with standard of care? 3. What are the effects of the ANC package on retaining women in ANC services? (Burkina Faso only)

Rwanda and Zambia
*Formative phase*
1. Adapt the WHO digital ANC module to the country-specific ANC package and local healthcare delivery context, customizing the ANC Digital Adaptation Kit (DAK) [36]
2. Identify bugs and errors in the clinical algorithms and in the country-adapted ANC digital module
3. Gather general feedback regarding the usability of the country-adapted ANC digital module and components for improvement
4. Develop and test training materials for the country-adapted ANC digital module
5. Develop and test supervision and technical support mechanisms for the country-adapted digital ANC module
*Demonstration phase—primary objectives*
1. Does the adherence to the country/state package of ANC interventions improve among health workers using the adapted WHO digital ANC module compared with standard care? a. Does the implementation of the country-specific ANC package (including targeted community mobilization) increase early initiation of ANC among pregnant women? 2. Is the use of the country-adapted WHO digital ANC module acceptable to, and does it create value for, women and health workers?
*Demonstration phase—secondary objectives*
1. What are the human resources training and supervision needs to ensure fidelity of deployment of the adapted WHO digital ANC module? 2. What are the financial resources needed to implement the adapted WHO digital ANC module for the study, and what resources would be needed to achieve scale?

## Methods: description

The proposed study is composed of two layers of interventions:The first refers to the ANC package adapted by each country or state (in India the study will be conducted in Assam and Tamil Nadu states). The adapted ANC packages are based on the WHO 2016 ANC recommendations. Each country or state adapted the WHO recommendations through a standardized process, which included conducting a situational analysis and stakeholder consultations to meet local needs and context. [19]The second refers to the co-interventions (or implementation strategies) to support the implementation of the adapted ANC package. The study’s co-interventions, the ‘how to’ components of changing health service provision [25], seek to modify the behaviour of both pregnant women and health workers, to ultimately improve ANC service provision. The co-interventions address findings from Downe et al.’s Cochrane review on qualitative evidence on the provision and uptake of routine ANC services [26]. In Rwanda and Zambia, this will include a digital health component.

### Logic model

A logic model was developed to specify the components of the co-interventions and how they are proposed or hypothesized to bring about changes in ANC service delivery (including improving implementation of the adapted ANC package) and uptake. We drew on the COM-B model of behaviour change and the related, Behavior Change Wheel, employed to conceptualize and describe the behaviour change targeted by the co-interventions [20]. COM-B proposes three necessary conditions for a desired behaviour to occur: (1) the person’s psychological and physical ability to perform it (capability – that is, having the necessary knowledge and skills), (2) their reflective and automatic mechanisms which ‘energize’ or prevent it (motivation – that is, strong intention to perform the behaviour, perceived importance, priority, advantages and disadvantages) and (3) the external social and environmental opportunity which enables or inhibits it (opportunity – that is, available resources, team culture and working norms) [20].

Each co-intervention addresses one of these conditions. Training health workers will build health workers’ capability through increasing knowledge, skills, and understanding of the adapted ANC package. Providing the necessary supplies and equipment will reduce barriers and increase health workers’ opportunity (physical) to implement the ANC package. In Rwanda and Zambia, employing the country-adapted digital module will support health workers’ capability, enabling them to adhere to the provision of the ANC package. Mentoring and supervision will provide hands on learning opportunities (social) and examples to imitate, as well as increase motivation through persuasion. Community mobilization will impact social influences on women, their families and key community stakeholders through persuasive communication. Better trained and supported health workers and available supplies aim to increase the positive experiences and perceptions that women have of ANC services, increasing their demand. Additionally, community-level messaging will focus on the importance of ANC seek to influence and encourage women and their families to access ANC early and more frequently. Figure 1 outlines and categorizes the four study co-interventions, linking them to the relevant COM-B domain and study outcomes.

**Fig. 1 Fig1:**
[figure not shown]
Study logic model. The colours in the third column are associated with either: capability (red), motivation (yellow) or opportunity (green). The purple box applies only to Rwanda and Zambia. COM-B: Capability Opportunity Motivation-Behavior ; BCW: Behavior change wheel

### Study design – India & Burkina Faso

The study design is a mixed methods stepped-wedge cluster randomized design implementation trial with nested cohort study (in India and Burkina Faso) (Fig. 2A). The design involves a sequential crossover of clusters from the control to the intervention arm, so that every cluster, composed of selected primary health facilities, begins in the control condition and eventually receives the intervention, with random assignment to the order of crossover.

**Fig. 2 Fig2:**
[figure not shown]
**A**, **B** Stepped-wedge cluster implementation designs. *Pkg* package, *ANC* antenatal care. The blue outlines refer to the nested cohort recruitment and follow up periods

Health facilities will be randomly allocated to one of four clusters. The study period of 24 months will be divided into six periods of four months each. All selected facilities will cycle through the following steps:Baseline phase: Facilities will all begin with at least one four-month period of baseline data collectionPreparation phase: This will be a transition phase where all the co-interventions will be initiated.Full implementation phase: Depending on the cluster [1–4], health facilities will implement the ANC package for a range of either one to four periods (4–16 months). Please see Fig. 2A for more information.

Implementation of the adapted ANC package will be done cluster wise from period 2 onwards, such that by period 6 all clusters would have received the intervention. Data will be collected cross-sectionally at the end of each month in each cluster.

In addition to collecting cross-sectional data in each cluster every period, two cohorts of pregnant women will be enrolled and followed through the course of their pregnancy. One cohort will not be exposed to the intervention (comparison arm). For the comparison group, pregnant women in cluster 1 and cluster 2 will be enrolled during the first three months of period 1 and followed through to the end of their pregnancy (period 3). For the intervention group, pregnant women in clusters 3 and 4 will be enrolled. To ensure comparability, for cluster 3, women will be enrolled during the first three months of period 4 and followed through to the end of their pregnancy (period 6), while for cluster 4, women will be identified and consented during the first three months of period 3 and followed through to the end of their pregnancy (period 5). Purposive sampling will be used to identify women coming for their first ANC during the first trimester. Research teams will monitor selection to ensure a balance in maternal age, parity, education level and religion.

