### Target population

Sub-national locations (i.e. region, state, districts, province, blocks) were selected in collaboration with the MoHs. For example, in some instances, the MoH considered locations with high or low performance^1^ on maternal and child health indicators to ensure that learnings will be applicable to settings with varying level of development. Generally, health facilities need to have a minimum volume of 30 women attending ANC once per month, human resource capacity of minimum two health workers providing ANC, and physical infrastructure (e.g. separate room dedicated to ANC service delivery).

Additionally, the following exclusion criteria were applied:Health facilities where the management does not agree to participate in the study,Health workers who do not consent (qualitative components),Women who do not provide consent (all study components),Women who do not reside in the catchment area of selected healthcare facilities (Burkina Faso and India),Women who also sought ANC services from non-public health platforms, such as the private sector (Rwanda),Girls under 14 years old (Burkina Faso & India),For the cohort study:women at more than 20 weeks of gestation,women with pre-identified complications.

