Additional outcomes will be measured using data collected through exit interviews (Rwanda and Zambia) and nested cohort study interviews (India and Burkina Faso) with pregnant women. This component will aim to assess the quality of ANC service provision (receipt of recommended evidence-based services), acceptability, and experience of care. To recruit women, health workers may conduct the first selection of potential participants while the country team will then follow up and gather informed consent. Health workers will not receive any remuneration for taking part in the study; therefore, they do not have an incentive to recruit participants. During the consent procedure it will be clearly explained to the women that participation is voluntary, and that their care will not be affected by their decision.

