#### For nested longitudinal data collection (India)

For estimating the sample size for the nested longitudinal study, the research team considered a secondary outcome indicator, that is, proportion of pregnant women whose blood pressure, weight and Hb are checked at least once in each trimester. As there are no reliable estimates for this indicator from either Tamil Nadu or Assam, we assumed it is approximately 50%. For our study to detect the relative risk within 20% of true value, which we assumed to be 1.25 (*P*1 = 62.5%), the computed sample size is 124. To account for clustering by health facility, we considered a design effect of 1.5, which leads to a sample size of 186. To account for loss to follow-up and the probability of some participants shifting to the private sector during the course of their pregnancy, we further inflated the sample by 25%, which leads to a sample size of 233. The country team rounded it up to 240 to equally distribute the sample across four health facilities of each arm (60 per health facility). Therefore, we will follow a total of 480 pregnant women, 240 during three consecutive non-intervention periods and 240 during three consecutive intervention periods through their pregnancy.

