#### For nested longitudinal data collection (Burkina Faso)

To estimate the sample size for the nested longitudinal study, we considered that only 81.7% of pregnant women attended at least one ANC contact [31]. The research team will consider an improvement of 10% with the intervention, that is, *P*1 = 91.4% and exposed/unexposed ratio = 1. The team considered a level of confidence of 95% and a power of 80%. The calculated sample size is 400. Considering the grouping by health facility, we considered a cluster effect of 1.5, which leads to a sample of 600. Accounting for the loss to follow-up of certain women, the country team further increased the sample by 10%, which leads to a sample size of 660 women (330 in each arm). The first 44 pregnant women who will come to each selected health facility for ANC after the start of the enrolment phase will be approached and invited to participate in the study.

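### Nested-cohort women are sampled purposively, possibly pre-selected by the staff whose care is assessed, so selection can differ between the comparison and intervention cohorts

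*Protocol article*

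**What the plan says.** All references are to the protocol article.

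- **Sampling method** (Study design – India & Burkina Faso, text after Fig. 2): "Purposive sampling will be used to identify women coming for their first ANC during the first trimester".
- **Safeguard** (same place): "Research teams will monitor selection to ensure a balance in maternal age, parity, education level and religion".
- **Who selects** (Quantitative data, paragraph on exit and cohort interviews): "To recruit women, health workers may conduct the first selection of potential participants while the country team will then follow up and gather informed consent". The reassurance offered is: "Health workers will not receive any remuneration for taking part in the study; therefore, they do not have an incentive to recruit participants". The same paragraph says these interviews assess the quality of the care provided, its acceptability and the experience of it.
- **When** (Study design – India & Burkina Faso): comparison women come from clusters 1 and 2 in period 1. Intervention women come from cluster 4 in period 3 and cluster 3 in period 4.
- **Other recruitment wording**: Study population and sample size has first-time attenders approached and invited, with no mention of purposive choice. The Burkina Faso cohort section invites "The first 44 pregnant women who will come to each selected health facility for ANC" once enrolment has started.
- **Gestational age**: the study design section and Table 5 set entry at a first contact in the first trimester. Target population lists, among the cohort exclusions, "women at more than 20 weeks of gestation". The two recruitment statements in the previous item give no trimester limit.

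**The concern.** Facilities are randomised to crossover order, but that protects the cohort comparison only if women enter the cohort by the same process in both arms. Here entry involves discretion. The people who may exercise it first are the health workers whose service provision is measured, and in the intervention arm they exercise it knowing that their facility is in the intervention condition.

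If staff in either arm lean towards women who seem likely to return, or who live nearby or are easy to follow, and do so to a different degree in the two arms, part of the cohort difference will reflect who was chosen rather than what the package did. Analysis cannot fully repair this afterwards, because the relevant traits are not recorded.

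The stated safeguards miss the mechanism. Absence of pay bears on whether staff recruit, not on whom they pick. Consent by the country team comes after the first selection. Balance on four recorded characteristics says nothing about motivation.

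**Working it through.** **1. Can selection differ by arm?** The text has every cluster pass through baseline, preparation and then one to four periods of implementation. Fig. 2A is not visible here, but the cohort timings fit an order in which cluster 4 crosses first:

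| Cluster | Baseline | Preparation | Implementation | Cohort enrolment |
|---|---|---|---|---|
| 4 | 1 | 2 | 3–6 | period 3, intervention |
| 3 | 1–2 | 3 | 4–6 | period 4, intervention |
| 2 | 1–3 | 4 | 5–6 | period 1, comparison |
| 1 | 1–4 | 5 | 6 | period 1, comparison |

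On this inferred order, every comparison woman is chosen before crossover and every intervention woman after it. The selectors' knowledge of the condition therefore coincides with arm.

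**2. Are the recruitment rules compatible?** A rule taking the first 44 women at a facility leaves no choice to the recruiter. A rule under which teams monitor selection to achieve balance presupposes choice. Both cannot govern the same Burkina Faso facility. For India, the study design section gives a purposive rule, the general sample-size section implies that first-time attenders are approached, and the India cohort section states no enrolment order.

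**3. Do the sample sizes allow for selection?**

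- *India*: precision of a relative risk, n = z²[(1−P1)/P1 + (1−P0)/P0] / [ln(1−0.2)]². With P1 = 0.625, P0 = 0.50 and z = 1.96, n = 123.4, so 124 per arm as stated. Then 124 × 1.5 = 186, and 186 × 1.25 = 232.5, so 233, rounded by the plan to 240.
- *Burkina Faso*: 81.7% v 91.4%, two-sided 5%, 80% power gives 194 per arm, 388 in total (428 with continuity correction), against 400 stated. Using 91.7% with the correction gives exactly 400. Then 400 × 1.5 = 600, and 600 × 1.1 = 660.

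The figures reproduce or come close. They allow for clustering and loss, not for selection, so they neither cause nor answer this point.

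**4. Sensitivity of the test to an assumed shift.** Suppose there is no true effect and selection alone raises the intervention cohort's rate by b. With p2 = p1 + b, p̄ their mean and n the effective number per arm:

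- SE0 = √[2p̄(1−p̄)/n]; SE1 = √[(p1(1−p1) + p2(1−p2))/n]
- P(reject) = 1 − Φ[(1.96·SE0 − b)/SE1] + Φ[(−1.96·SE0 − b)/SE1]

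Inputs are 240/1.5 = 160 per arm for one Indian state (186/1.5 = 124 after the planned loss) at a 50% base, and 300/1.5 = 200 per arm for Burkina Faso at an 81.7% base. Women recruited at a contact have all attended at least one, so 81.7% serves here only as the plan's own sizing input.

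| Assumed net shift (points) | India, n = 160 | India, n = 124 | Burkina Faso, n = 200 |
|---|---|---|---|
| 0 | 5% | 5% | 5% |
| 2.5 | 7% | 7% | 10% |
| 5 | 15% | 12% | 28% |
| 7.5 | 27% | 22% | 57% |
| 10 | 44% | 35% | not run |

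The shifts are assumptions. The table shows how sensitive the comparison is, not how biased it will be.

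**The case against.** The case on the other side is substantial.

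- *Health-worker selection is permitted, not prescribed.* The wording is permissive, the country team takes consent and research teams monitor the process. This stands as a limit on certainty. It does not remove the opening for arm-dependent choice.
- *Purposive may only mean criterion-based*, that is, a first contact in the first trimester, with the first-44 rule as its operational form. This is plausible for Burkina Faso. It sits badly with the balance rule, and India has no stated consecutive rule to fall back on.
- *The same procedure applies in both arms, and care is observed in both.* Correct: only differential selection biases the contrast, and the document does not show that it will occur, or in which direction.
- *The cohort is not the main comparison.* Its interviews supply additional outcomes, and India sized it on a secondary one. The register-based stepped-wedge analysis does not pass through this selection.

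A reader might go further and infer that the gestational-age limits contradict each other. On that reading, women at 13 to 20 weeks would be enrolled and would fail India's sizing outcome ("blood pressure, weight and Hb are checked at least once in each trimester") whatever their later care. The document does not support this. First-trimester entry is stated twice, and a woman must meet the entry criterion as well as escape the exclusions. The 20-week line is therefore redundant, and the failure arises only if the entry criterion is set aside. A reader might likewise attach a number of points to the bias by assuming a share of favoured women and their chance of the outcome. Any such figure comes from the chosen inputs and from supposing that selection occurs in one arm only.

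**Conclusion.** The concern holds as a design weakness of the nested cohort. A purposive rule, possible pre-selection by assessed and unblinded staff, and enrolment before crossover in one arm but after it in the other allow selection to differ by arm. Monitoring four measured characteristics cannot exclude that. The recruitment statements also disagree and need reconciling. The 20-week exclusion and the missing trimester limits call for tidying rather than showing a second eligibility window.

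Size and direction cannot be derived. The rejection rates in the working are conditional on assumed net shifts, on the plan's base rates and on its design effect of 1.5. It would be wrong to conclude that bias is established, or that the register-based stepped-wedge outcomes are compromised. The article states these enrolment rules itself, and a later analysis plan could adjust for recorded covariates but could not undo how the women were chosen. The change should be made.

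**What to change.** 1. Replace purposive sampling with consecutive enrolment, in both arms and both countries, of every eligible woman at her first ANC contact in the first trimester until the facility quota is filled.
2. Have the research team identify women from the register, with a screening log of those eligible, approached, declined and enrolled. Remove first selection by health workers for the cohort. The Burkina Faso rule counts women approached, so state whether the quota means approached or enrolled.
3. Drop balancing by selection. Adjust for age, parity, education and religion in the cohort analysis.
4. Reconcile the 20-week exclusion in Target population, and the missing trimester limit in the general sample-size and Burkina Faso cohort sections, with the first-trimester entry criterion.

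The cost is protocol wording and a log. No sample size changes. Covariate balance is no longer forced, and quotas may fill more slowly. For example, assume 30 first contacts a month (the register abstraction figure) and Burkina Faso's 40% before 12 weeks: 30 × 0.40 = 12 eligible a month, or 36 in three months against 44 needed, so about 44/12 = 3.7 months before refusals. In India, 60 of 90 first contacts (67%) would have to be in the first trimester. Busier facilities would fill sooner, and Study population and sample size already allows enrolment to be extended.

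One limit should be stated in the protocol. The package aims to bring women to care earlier, so first-trimester attendance is itself affected by it. Cohort composition may still differ by arm under consecutive enrolment. The change removes discretionary choice, not that source of difference.
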